### Randomization

After the initial assessment and compliance with eligibility criteria, participants will be randomized into two intervention group [patients achieving diurnal hemodialysis and nocturnal hemodialysis] and the control group [CKD not submitted to dialysis]. Randomization numbers will be generated using a randomization table at a central office. A series of numbered, sealed, opaque envelopes will be used to ensure confidentiality. Each envelope will contain a card stipulating to which group the subject will be allocated.All patients underwent randomization protocol that will meet the eligibility criteria and be clinically stable.

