### Sample size calculation and statistical analysis

According to the findings of a previously published epidemiological study [17] that the proportion of adults with an apnea/hypopnoea index (AHI) ≥ 15 corresponds to 16.9% of the Brazilian population and that of a previous study [18] that AHI ≥ 15 had an approximately 50% prevalence rate in patients with CKD undergoing conventional dialysis (3 times a week, 4 h per session) [19], the sample size was calculated as 57 patients, with an *α* = 0.05 and *β* = 90% (test power).

The Kolmogorov–Smirnov normality test will first be performed to determine whether a normal distribution sample is present. A descriptive analysis will be performed, with the data expressed as either mean and standard deviation or median values and 95% confidence intervals, as appropriate. One-way analysis of variance will be used for comparisons between work shifts once the samples have a normal distribution. V_0.2_ and ΔV (%) values will be linearly correlated with the AHI, for which either the Pearson or Spearman correlation test will be used, depending on the sample distribution. Either the non-paired Student *t* test or Mann–Whitney test will be used for comparisons between individuals with and those without OSA.

In addition, a logistic regression analysis of continuous factors with categorical responses will be performed. Receiver operating characteristic (ROC) curves will be constructed to determine the sensitivity (true-positive rate) versus 100% specificity (false-positive rate) at various levels of the measured $\Delta \dot{V}$ (%) and V_0.2_ (%) to identify the cut-off value yielding the largest number of correctly classified patients. The statistical analysis will be performed by an experienced statistician using the JMP version 8.0 (SAS/STAT® Software, SAS Institute Inc., Cary, NC, USA) and SPSS version 16.0 programs (Somers NY). A 5% level of significance and 95% confidence interval will be applied.

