### Evaluation protocol

#### Clinical evaluation

Patients with chronic kidney diseases and end-stage renal disease undergoing dialysis, based on recommended procedures, will be submitted to general physical measurements performed by a well-trained physician and physical therapist before and after the dialysis session using precise instruments. The measurement protocol will include body weight (kg); height (cm); body mass index (BMI) calculated using the formula weight/height^2^[16]; circumferences (cm) of the neck, waist, and hip [20]; heart and respiratory rates; blood pressures; Mallampati index [21]; tonsil index [22]; heart rate variability [23]; maximum ventilatory pressure; negative expiratory pressure (NEP) test; and polysomnography (PSG; sleep study), as well as the administration of specific questionnaires addressing sleep apnea, excessive daytime sleepiness [24,25], symptoms of stress [12], and depression [12-14], anxiety [15], and quality of life [26,27].

The following data will be obtained from medical charts: biochemical values, associated pathological conditions, laboratory values (iron, intact-parathyroid hormone, haemoglobin, calcium, phosphorus, and creatinine), duration of dialysis therapy, comorbidities, and aetiology of kidney disease.

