### Study interventions

#### Haemodialysis

Regular daytime or nocturnal haemodialysis was standardised during the trial. It was performed 3 times per week, with a 4-h session duration, 250-mL/min blood flow, and 500-mL/min dialysate flow, using bicarbonate-buffered dialysate with 1.25 mmol/L ionised calcium concentration, dialysate temperature of 36.5°C, and Polyflux 17-L dialyser [42].

The ultrafiltration amount for each haemodialysis session was decided by individual dry weight, which was fixed during the trial. In addition, during the trial, the patients were not permitted to change their medication or start new drugs, especially antiplatelet agents, angiotensin-converting enzyme inhibitors, angiotensin II receptor antagonists, calcium-channel blockers, and β-blockers.

The patients who required a change in medication for medical reasons were subsequently excluded from the study. Use of *N*-acetylcysteine was also prohibited in view of its potential influence on ischemia-reperfusion injury.

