## Discussion

CKD is a major public health problem worldwide, and its incidence has increased in part by the increased life expectancy and increasing number of cases of diabetes mellitus and hypertension. Sleep disorders are common in patients with renal insufficiency and is much more prevalent in patients with end-stage renal disease than in the general population [4].

Symptomatic obstructive sleep apnoea syndrome has been related to be a risk factor for hypertension, heart failure and vascular dysfunction, and has been proposed to be causally related to both non-fatal and fatal coronary and cerebrovascular events [43]. Moreover, renal chronic patients frequently presented restless legs syndrome that also is associated with higher mortality and elevated incidence of cardiovascular events [44]. Thus, once presence of OSA also seems to reduce quality of haemodialysis [45] it’s incorrectly identification among CKD patients may lead to worst outcomes or fail of hypertension control [46].

Our hypothesis is that the weather weight gain due to volume overload observed during interdialytic period will influence the degree of collapsibility of the upper airway due to narrowing and predispose to upper airway occlusion during sleep, and to investigate the influences of different shifts haemodialysis in the physiological variables of sleep and ANS activity, and respiratory mechanics, and depression, anxiety, stress and quality of life in end-stage renal disease patients. With our proposed study, we intend to identify the main factors that cause sleep disorders in patients with CKD that lead to the identification of the best treatment to reduce mortality and improve the quality of life of these patients.

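### Patients who need a medication change after randomisation are excluded from the study; this can bias the comparison of the randomised groups, by an amount and in a direction the document does not allow one to determine

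*Protocol article*

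**What the plan says.** Under Randomization, allocation comes once eligibility is settled: "After the initial assessment and compliance with eligibility criteria, participants will be randomized". The same sentence defines three groups: "participants will be randomized into two intervention group [patients achieving diurnal hemodialysis and nocturnal hemodialysis] and the control group [CKD not submitted to dialysis".

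Under Haemodialysis, the article restricts drugs after that point: "during the trial, the patients were not permitted to change their medication or start new drugs, especially antiplatelet agents". The list goes on to ACE inhibitors, angiotensin II antagonists, calcium-channel blockers and β-blockers. The consequence of needing a change is: "The patients who required a change in medication for medical reasons were subsequently excluded from the study". This rule is separate from the eligibility exclusions listed under Subjects.

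Three other places bear on the point:
- Clinical evaluation lists among the measurements "heart and respiratory rates; blood pressures; Mallampati index [21]; tonsil index [22]; heart rate variability [23".
- The Discussion says that unrecognised sleep apnoea in these patients "may lead to worst outcomes or fail of hypertension control".
- Sample size calculation and statistical analysis gives the size: "the sample size was calculated as 57 patients". It does not say whether this is the total or per arm, and it mentions no allowance for exclusions.

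The article nowhere says that excluded patients are still assessed, or that they are analysed in their allocated group.

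**The concern.** Randomisation makes groups comparable only while the randomised patients are kept. Here patients leave because of a clinical event that occurs after allocation and that the allocated group may influence. The document itself makes that plausible:

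- The named drugs act mainly on the cardiovascular system, and cardiovascular and autonomic variables are among the outcomes.
- The Aims section holds that fluid gain between dialysis sessions affects upper airway collapse. The dialysis groups have fluid removed by ultrafiltration and the control group does not, so the need for a medication change could differ between groups.
- The Discussion ties sleep apnoea to poor control of hypertension, and AHI is the variable on which the sample size rests.

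If leaving depends on both group and outcome, the patients who remain no longer give a fair comparison. A second, smaller matter is lost numbers. If patients stop being assessed, no later analysis plan can recover their outcomes.

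**Working it through.** **1. Timing.** Eligibility and initial assessment come first, then randomisation, then the medication restriction for the duration of the trial, then exclusion of those who need a change. The exclusion is therefore after allocation on the article's own wording.

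**2. When the comparison is biased.** Let π be the true prevalence of AHI ≥ 15 in a group, e₁ the proportion excluded among patients with AHI ≥ 15, and e₀ the proportion excluded among the others. The prevalence among those who remain is

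π(1 − e₁) / [π(1 − e₁) + (1 − π)(1 − e₀)].

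The document gives no exclusion rates, so every e below is an assumption. Take π = 0.5 in both groups, so that there is no true difference. In rows 1 to 3 and row 5 the comparison group loses 10% of each kind (e₁ = e₀ = 0.10) and stays at 50%.

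| Row | e₁ / e₀ in the affected group | Observed prevalence | Comparison group | Spurious difference |
|---|---|---|---|---|
| 1 | 0.20 / 0.10 | 0.40/(0.40 + 0.45) = 47.1% | 50% | −2.9 points |
| 2 | 0.30 / 0.10 | 0.35/(0.35 + 0.45) = 43.8% | 50% | −6.3 points |
| 3 | 0.40 / 0.10 | 0.30/(0.30 + 0.45) = 40.0% | 50% | −10.0 points |
| 4 | 0.20 / 0.10 in both groups | 47.1% | 47.1% | 0 |
| 5 | 0.10 / 0.30 | 0.45/(0.45 + 0.35) = 56.3% | 50% | +6.3 points |

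Row 4 shows that identical exclusion shifts both prevalences but leaves the difference at zero. Row 5 shows that the sign reverses if the patients who change medication are mostly those with AHI < 15.

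**3. The stated sample size.** Inputs from the article: p₁ = 0.169 (the proportion that "corresponds to 16.9% of the Brazilian population"), p₂ = 0.50 in conventional dialysis patients, α = 0.05, power 90%. With p̄ = 0.3345 and a two-sided test, n per group is

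[1.96·√(2·0.3345·0.6655) + 1.2816·√(0.169·0.831 + 0.5·0.5)]² / 0.331² = 40.6, so 41 per group.

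That is 82 for two groups and 123 for three. The figure of 57 is not reproduced at 90% power. That is a separate matter, but it means that one cannot tell from the calculation whether 57 is a total or a per-arm number.

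**4. Power after exclusions.** The contrast is 16.9% against 50%, two-sided 5%. The loss is a new assumption, the same in every group, and is not the loss used in step 2.

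| Reading of 57 | Per group | Power, no loss | Per group after loss | Power after loss |
|---|---|---|---|---|
| Total, 1:1:1 (both assumed) | 19 | 61.9% | 15 (4 lost, 21%) | 50.9% |
| Per arm | 57 | 97.2% | 45.6 (20% lost) | 93.1% |

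The first row is exact power of the uncorrected chi-square test. The second uses the normal approximation, which for 19 per group gives 58.6%, falling to 48.9% at 20% loss.

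If 57 evaluable patients are needed, enrolment would be 57/0.9 = 64 at 10% exclusion and 57/0.8 = 72 at 20% (rounded up; rates assumed).

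**The case against.** The strongest reply is that the harm is plausible but not shown. The article gives no exclusion rate, overall, by group or by AHI, and no trial duration, so nobody can say how many patients the rule would reach. A reader might infer that exclusion is in fact tied to group and outcome, or that the bias favours the group with more medication changes. The document supports neither. The direction depends on which patients change medication, and with identical exclusion in every group the difference is undistorted.

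The power loss is also conditional. A reader might conclude that the sample is too small and that the exclusions make it worse. That needs 57 to be the total and allocation to be equal, and the article states neither. Moreover, 16.9% against 50% sets the general population against dialysis patients and is not a stated contrast between the randomised groups. Even on the total reading, most of the gap to 90% exists before anyone is excluded.

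Much of the planned analysis (correlations with AHI, comparison of patients with and without OSA, logistic regression, ROC curves) does not compare randomised groups. There the rule raises a question of selection rather than of broken randomisation.

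Finally, an unseen analysis plan might define an all-randomised set, and exclusion from the study might mean only that participation stops. This helps little. On either meaning outcomes after the change are lost, and the article states the exclusion outright.

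These points limit how much can be claimed about size and direction. They do not remove the defect in the rule.

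**Conclusion.** The concern stands in conditional form. The article sets an exclusion after randomisation that can depend on both group and outcome, and so can bias comparisons between the randomised groups. The size and direction of any bias cannot be determined from the document. The 6.3-point spurious difference (2.9 to 10.0 points across the assumed range) shows what moderate differential exclusion would do; it is not an estimate for this trial.

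The loss of numbers is secondary and depends on the reading of 57: pairwise power falls from 62% to 51% if 57 is the total split equally and 4 of 19 are lost per group, but stays at about 93% at 20% loss if 57 is per arm. The documents do not support a firm statement that the bias favours a particular group, or that the trial is underpowered because of this rule.

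**What to change.** Leave the medication restriction as written; this point takes no view on it. Replace only the exclusion sentence, for example: *Patients whose medication changes for medical reasons remain in the study, continue all scheduled assessments and are analysed in the group to which they were randomised; the date and the drug are recorded.*

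Make the all-randomised set primary for between-group comparisons, and report the analysis without patients who changed medication as a sensitivity analysis only.

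The cost is one sentence, a few more scheduled assessments, and possibly a slight dilution of the estimated effect, because some patients will be assessed after a change of drug. The sensitivity analysis would show how far the result depends on these patients.

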#### Quality control

To ensure the quality of the data, the physiotherapists and physicians in charge of data collection will receive specific training. Periodic external monitoring will be performed to verify the adequate application of methodology in performing examinations and data collection.

## Discussion

CKD is a major public health problem worldwide, and its incidence has increased in part by the increased life expectancy and increasing number of cases of diabetes mellitus and hypertension. Sleep disorders are common in patients with renal insufficiency and is much more prevalent in patients with end-stage renal disease than in the general population [4].

Symptomatic obstructive sleep apnoea syndrome has been related to be a risk factor for hypertension, heart failure and vascular dysfunction, and has been proposed to be causally related to both non-fatal and fatal coronary and cerebrovascular events [43]. Moreover, renal chronic patients frequently presented restless legs syndrome that also is associated with higher mortality and elevated incidence of cardiovascular events [44]. Thus, once presence of OSA also seems to reduce quality of haemodialysis [45] it’s incorrectly identification among CKD patients may lead to worst outcomes or fail of hypertension control [46].

Our hypothesis is that the weather weight gain due to volume overload observed during interdialytic period will influence the degree of collapsibility of the upper airway due to narrowing and predispose to upper airway occlusion during sleep, and to investigate the influences of different shifts haemodialysis in the physiological variables of sleep and ANS activity, and respiratory mechanics, and depression, anxiety, stress and quality of life in end-stage renal disease patients. With our proposed study, we intend to identify the main factors that cause sleep disorders in patients with CKD that lead to the identification of the best treatment to reduce mortality and improve the quality of life of these patients.
